#### Secondary outcomes

1. Severity of PTS between groups

2. Bleeding events - defined as in Table 2

3. INR control in terms of percentage time in range

4. Optimal cut off on a D-dimer result

5. Costs of D-dimer and subsequent extended treatment with anticoagulation

6. Cost effectiveness

7. Information on the types of patient who potentially benefit from extended warfarin treatment, age and gender

8. Patient quality of life

**Table 2 T2:** Definition of bleeding events

**Major bleeding**	Clinically overt bleeding that is associated with:
	A fall in haemoglobin of 2 g/dl or more, or
	A transfusion of 2 or more units of packed red blood cells or whole blood, or
	A critical site: intracranial, intraspinal, intraocular, pericardial, intra-articular, intramuscular with compartment syndrome, retroperitoneal, or
	A fatal outcome
**Non-major clinically relevant bleeding**	Non-major clinically relevant bleeding is defined as overt bleeding not meeting the criteria for major bleeding but associated with medical intervention, unscheduled contact (visit or telephone call) with a clinician, (temporary) cessation of warfarin treatment, or associated with discomfort for the subject such as pain or impairment of activities of daily life.
	Examples of non-major clinically relevant bleeding are:
	• Epistaxis if it lasts for more than 5 minutes, if it is repetitive (i.e., 2 or more episodes of true bleeding, i.e., not spots on a handkerchief, within 24 hours), or leads to an intervention (packing, electrocautery, etc.) and no admission to hospital.
	• Gingival bleeding if it occurs spontaneously (i.e., unrelated to tooth brushing or eating), or if it lasts for more than 5 minutes
	• Haematuria if it is macroscopic, and either spontaneous or lasts for more than 24 hours after instrumentation (e.g., catheter placement or surgery) of the urogenital tract
	• Macroscopic gastrointestinal haemorrhage: at least 1 episode of melena or hematemesis, if clinically apparent
	• Rectal blood loss, if more than a few spots
	• Haemoptysis, if more than a few speckles in the sputum, or
	• Intramuscular hematoma
	• Subcutaneous hematoma if the size is larger than 25 cm^2^ or larger than 100 cm^2^ if provoked

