Total sample size will be sufficiently large to show a significant difference in recurrence rates between those showing a positive D-dimer on treatment who receive warfarin (RW) and those showing a positive D-dimer who receive no treatment (RNO plus RRO). Following Palareti [7] this means a sample size for each group of 79 in order to give 90% power to a 5% significance test when comparing 2 year recurrence rates of 21.4% and 4.3%. Assuming a 50% positive D-dimer rate this implies a total of 79 × 2 × 2/0.9 = 352 patients taking part in the study (and 316 completing the study). Allowing a 50% participation rate this means that 704 patients need to be approached initially. With such a sample size an overall comparison of recurrence rates between the arms W and O can be made with power of between 86 and 99% assuming recurrence rates of between 1.4% and 4.3% for the warfarin arm (Group W, depending on what recurrence rate patients with normal D-dimer on warfarin produce) and 14.2% for the No treatment arm.

One of the objectives of the study is to determine an optimal cut off on a D-dimer result taken when the patient is receiving treatment. In a study of 272 patients, Baglin *et al.* report that 170/272 patients had a D-dimer in excess of 500 ng mL-1 and their ROC analysis suggests an optimal cut off of 500 ng/ml [10]. The circumstances of their study differ from ours but using their data will give some indication of the precision with which we will be able to estimate an optimal cut off with slightly more patients than Baglin *et al.* With some assumptions, a rough calculation of the precision with which a cut off in the region of 500 could be estimated with our sample size of 316 would be within about 7% (95% confidence interval).

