### Analysis and statistical methods

Intention to treat analysis will be used. The types of analysis proposed are Chi-square, generalized linear models, logistic regression and survival analysis, t-tests, ANOVA and non-parametric equivalents.

Analysis will be carried out at the end of the study, as there is likely to be insufficient power for interim analyses. Quality control of data collection will be conducted by a trial management committee throughout the study and by a statistician independent of the research team.

Logistic regression would be used to relate D-dimer result and other patient data to events such as recurrence, bleeding episodes and PTS separately on the two arms (Group W and Group O) of the trial and together. Baglin *et al*[10], with their 272 patients, showed a significant association between age and D- dimer (p < 0.001) and our total sample, allowing for loss to follow up, of 316 should be ample to incorporate such a relationship. In comparing D-dimer levels between genders they achieved a significance level of p = 0.18 with 272 individuals. A rough calculation would suggest a p value of 0. 15 for the same level of difference in D-dimer (approximately 80 ng/ml) in our total sample of 316 patients.

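### The stated precision of about 7% for the optimal on-treatment D-dimer cut-off is tied to 316 patients, but a cut-off that discriminates recurrence rests on about 22 recurrences

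*Protocol article*

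**What the plan says.** Under Sample size, the protocol article sets out to "determine an optimal cut off on a D-dimer result taken when the patient is receiving treatment". It takes its starting point from a cited cohort of 272 patients, in which "170/272 patients had a D-dimer in excess of 500 ng mL-1". For the threshold itself it relies on the same cohort's discrimination analysis: "their ROC analysis suggests an optimal cut off of 500 ng/ml". It notes that this cohort's circumstances differ and that the trial will have slightly more patients. It then reports the result of a rough calculation, made with some assumptions: "a cut off in the region of 500 could be estimated with our sample size of 316 would be within about 7" per cent, labelled as a 95% confidence interval. Neither the formula nor the assumed spread of D-dimer is given, and the number of recurrences is not mentioned.

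The cut-off is a named deliverable: item 4 of the Secondary outcomes is "Optimal cut off on a D-dimer result".

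The same Sample size section supplies the event rates. It assumes 316 completers, a 50% D-dimer positive rate, two-year recurrence of 14.2% in the no-treatment arm, and 1.4% to 4.3% on warfarin.

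**The concern.** A cut-off taken from an ROC analysis is the value that best separates those who recur from those who do not. Its sampling error is governed mainly by the smaller of the two classes, not by the total number enrolled. An on-treatment D-dimer meant to guide stopping has to predict recurrence after stopping, so most of the information lies in the no-treatment arm. The article compares itself with the cited cohort by number of patients only.

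A reader told to expect +/-7% around 500 ng/ml (about 465 to 535) would take the trial's cut-off as close to definitive. If the real uncertainty is several times larger, the trial may deliver a threshold that another sample of the same size would move substantially. That matters for the prediction algorithm listed among the aims and for the use of point-of-care D-dimer testing in primary care.

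**Working it through.** **Inputs from the article (Sample size).** 79 per D-dimer-positive group; recurrence 21.4% untreated and 4.3% on warfarin in D-dimer positives; 50% positive; 316 completers, so 158 per arm; 14.2% recurrence in Group O; 1.4% to 4.3% in Group W; 170/272 = 62.5% above 500 ng/ml in the cited cohort.

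**Assumption, not in the article.** D-dimer is log-normal with log-SD 0.5, with 0.8 as a sensitivity value.

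**Step 1: the surrounding figures.** A two-sided 5% test of 21.4% against 4.3% with 90% power needs 79 per group. 79 x 2 x 2/0.9 = 351.1, against 352 stated. Power for Group W against Group O with 158 per arm is 99.1% at 1.4% and 86.3% at 4.3%. All of these agree with the article.

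**Step 2: the 7%.** It cannot be reproduced without adding an assumption. Three natural candidates with n = 316 are:
- Half-width of the proportion 170/272: 1.96 x sqrt(0.625 x 0.375/316) = 5.3 points, or 8.5% relative.
- A mean, with the SD of about 492 ng/ml implied by the gender comparison under Analysis and statistical methods (80 ng/ml, p = 0.18, equal groups assumed): 1.96 x 492/sqrt(316) = 54, or 10.9% of 500.
- A fixed percentile of D-dimer (the 37.5th): 1.96 x sqrt(0.375 x 0.625/316)/0.379 x log-SD = 7.0% at log-SD 0.5 and 11.3% at 0.8.

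The third can give 7%, but only at one assumed spread. None of the three uses recurrence data.

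**Step 3: expected recurrences.** Group O: 158 x 0.142 = 22.4. Group W: 158 x 0.014 = 2.2 to 158 x 0.043 = 6.8. Both arms: about 25 to 29.

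**Step 4: separation implied by the article's rates.** Risk in D-dimer negatives = (14.2 - 0.5 x 21.4)/0.5 = 7.0%. Sensitivity at the cut-off = 0.5 x 0.214/0.142 = 75%. Specificity = 0.5 x 0.930/0.858 = 54%. Youden index J = 0.754 + 0.542 - 1 = 0.295. With two equal-variance normals, d = 2 x inverse-normal((1 + J)/2) = 0.76 SD.

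**Step 5: 95% range of the estimated optimum.** Log-SD 0.5; the binormal rows use 22 recurrences and 136 non-recurrences, d = 0.76.

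| Estimator and set-up | 95% range |
|---|---|
| Empirical Youden, risk steps from 7.0% to 21.4% at 500, n = 158 | about 401 to 754 ng/ml (-20% to +51%) |
| Empirical Youden, binormal | -33% to +58% |
| Kernel-smoothed, binormal | -28% to +49% |
| Binormal fit, unequal variances | -22% to +23% |
| Binormal fit, equal variances forced | -11% to +12% |

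The first four rows are simulations. The last can be checked by hand, because the optimum is then the midpoint of the two means: 1.96 x 0.5 x 0.5 x sqrt(1/22 + 1/136) = 0.113 on the log scale, or -11% to +12%.

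**Step 6: sensitivity.**
- Pooling both arms (26 recurrences in 316) gives -30% to +56% for the empirical optimum.
- Over d = 0.5 to 1.5 the empirical range in Group O runs from -37%/+71% to -24%/+43%.
- At log-SD 0.8 the empirical range is -46% to +109%, and the equal-variance range -16% to +20%.
- Whatever the cut-off, sensitivity estimated from 22 recurrences carries +/-1.96 x sqrt(0.7535 x 0.2465/22) = +/-18 points.

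**The case against.** **The article hedges.** It calls the calculation rough, says that assumptions were made, and warns that the cited cohort differs. That stands as a warning about inputs. It does not tell the reader that precision depends on recurrences, which are about one in seven of the Group O completers.

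**The multiple depends on the estimator.** This stands. The article fixes no search method for the cut-off, and it plans logistic regression for relating D-dimer to recurrence. A strongly parametric approach loses much less: about 1.6 times the stated figure under forced equal variances. Under that model 7% could be reached with a small enough spread, since ln(1.07)/(1.96 x 0.5 x sqrt(1/22 + 1/136)) gives a log-SD of about 0.30. But a log-normal with log-SD 0.30 and 62.5% of values above 500 has an SD of about 177 ng/ml, against the roughly 492 implied by the article's gender comparison (equal groups assumed). No single range, including -20% to +50%, should be put forward as the best case.

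**Stronger readings that a reader might infer, and that the documents do not support:**
- *The 7% was computed as the precision of a percentile.* The match in Step 2 depends on an assumed spread, and the article shows no derivation.
- *The primary comparison of raised against normal D-dimer off treatment (RO against NO) has an inflated type I error because the cut-off is optimised.* The optimum is sought on the on-treatment sample. That comparison uses a separate sample taken one month after stopping, and nothing says the optimum will label the groups. With no true association, applying an on-treatment Youden cut-off to a correlated off-treatment value rejects about 5% to 6% of the time for correlations from 0 to 0.9. Rejection near 23% arises only if the same measurement is both optimised and tested.
- *The article calls its numbers ample for recurrence.* The sentence "our total sample, allowing for loss to follow up, of 316 should be ample to incorporate such a relationship" is about age and D-dimer, for which every patient contributes.

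The absence of a numeric threshold for raised and normal is detail that an article can leave to the full protocol or analysis plan.

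**Conclusion.** The concern holds in a limited form. A 95% precision of about 7% for an optimal cut-off is not supported by the article's own event rates, which give about 22 recurrences off treatment and 25 to 29 in all. At log-SD 0.5, an ROC-type optimum, the kind the article cites, has limits about 3 to 8 times as far from the estimate as stated. An unequal-variance binormal fit is about 3 times as wide, and the most favourable model tried about 1.6 times.

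The event counts follow directly from the article. The ranges rest on an assumed log-normal shape and spread, and on a separation inferred from the 21.4%, 14.2% and 50% figures.

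The consequence is confined to a secondary outcome and to how firmly its result may be read. The planned comparison of recurrence rates, with "a sample size for each group of 79 in order to give 90% power to a 5% significance test" and 352 patients in total, does not depend on the 7%.

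**What to change.** Under Sample size, replace the 7% with a precision statement based on the expected recurrences: about 22 in Group O, with 2 to 7 more under warfarin. Name the estimator, state the assumed spread of D-dimer and its source, and show the range over plausible spreads rather than one figure. State that the optimum is exploratory, is derived mainly from Group O, and will be reported with a bootstrap interval.

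The cost is a change of wording, a routine bootstrap and a less favourable precision figure. No change to recruitment, visits or the primary analysis is needed.

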### Randomisation

Randomisation will be performed within the computerised clinical case report form (CRF) produced in Primary Care Clinical Sciences, University of Birmingham. When a patient is identified as being eligible for the study and has given written consent to take part, the research nurse will enter details into the computerised CRF and will be issued immediately with a dedicated randomisation code allocating the patient to either continuing warfarin therapy or stopping warfarin therapy.

Patients will be randomly allocated at this point to either continue warfarin (Group W) for a further 2 years or to discontinue treatment (Group O). Randomisation will be stratified by DVT and PE to ensure there are equal numbers in both groups W and O.

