### Trial intervention

Study participants will have a total of six visits over a two year period.

#### Visit 1

This is the same visit as the information, consent and randomisation visit and will be within 2 weeks of current anticoagulation treatment end date. Patients will be randomised electronically into one of two groups; Group O will discontinue warfarin after their usual clinical intervention, Group W will continue warfarin for a further two years.

Patients will be interviewed to collect the following data:

Concomitant medications; ethnicity; smoking status; alcohol consumption; medical history; BMI; and family history of VTE

A heparinised venous sample of blood will be taken for a D-dimer test on a POC device (Cobas h 232, Roche diagnostics). In addition citrated venous samples will be collected for D-dimer testing. These will be sent to a central laboratory to be frozen and stored for analysis during and at the end of the study.

The D-dimer result will be recorded centrally onto a database for future analysis and both patient and researcher will be blinded as to the result of this test.

All patients will be clinically examined for signs and symptoms of PTS using a validated clinical scoring system (the Villalta scale) and will also complete the VEINES quality of life score [24] as well as EQ 5D which allows the measurement of broad aspects of quality of life [25]. In addition the patients will complete a costs questionnaire relating to the expenses incurred on a recent anticoagulation clinic visit. Where questionnaires are incomplete or unclear the patients will be contacted by telephone to clarify and complete the responses.

Compression stockings will be used by patients as advised by the clinician treating the DVT and the researchers will not influence their utilisation.

The anticoagulation clinic that the patient would normally attend will be informed that the patient is entering a study as will any specific hospital consultants who are involved with the patients’ care (e.g. haematologists). Patients randomly allocated to Group W will be followed-up through their usual oral anticoagulation service provided in terms of warfarin management and the anticoagulation clinic lead will be asked to extend their clinic visits for a further 2 years. Patients randomly allocated at this point to Group O will undergo a further D-dimer test 1 month after cessation of treatment. Again both researcher and patient will be blinded to this result.

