### Assessment of safety

Participants safety will be ensured by screening for eligibility using a structured form completed by trial healthcare professionals. This will record evidence of eligibility and the presence/absence of any inclusion and exclusion criteria. The Research Associates and Nurses will take a general medical and drug history to assess for other complicating diseases and medications. Any queries will be discussed with the trial nurse, chief investigator and the relevant physicians at the trial site. The eligibility will be signed off by the physician providing routine medical care.

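### The open allocation can be revealed before the visit 1 Villalta, VEINES and EQ-5D baselines are recorded, because nothing requires them to be completed first

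*Protocol article*

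**What the plan says.** The Randomisation section gives two conditions for allocation: "When a patient is identified as being eligible for the study and has given written consent to take part". Then "the research nurse will enter details into the computerised CRF and will be issued immediately with a dedicated randomisation code". It does not list what the details are.

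Under Trial intervention, Visit 1, everything happens on one occasion: "This is the same visit as the information, consent and randomisation visit and will be within 2 weeks of current anticoagulation treatment end date". The section goes on: "Patients will be randomised electronically into one of two groups". Only after that does it say "Patients will be interviewed to collect the following data", a list that includes concomitant medications and medical history. The blood samples follow, and then "All patients will be clinically examined for signs and symptoms of PTS using a validated clinical scoring system", with VEINES, EQ-5D and a costs questionnaire. The section closes with "Patients randomly allocated at this point to Group O will undergo a further D-dimer test 1 month after cessation of treatment".

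The only blinding described at visit 1 is of the D-dimer result. No placebo is described, and the nurse receives the code.

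On eligibility, the Participants section has the primary care notes checked before the first visit is arranged. Assessment of safety adds a structured form, sign-off by a physician, and this: "The Research Associates and Nurses will take a general medical and drug history to assess for other complicating diseases and medications".

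**The concern.** A baseline is useful because it cannot have been affected by the treatment arm. Villalta includes symptoms, and VEINES and EQ-5D are self-reported. A patient who has just been told to stop or to stay on warfarin may answer differently, and a nurse who knows the arm may score differently.

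These measures carry real weight in this trial. Reducing PTS is part of the first aim, and separating new PTS from PTS already present needs a clean baseline Villalta score. Quality of life is a secondary outcome, and EQ-5D feeds the cost-utility analysis. A baseline collected with the arm known cannot be repaired in the analysis.

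There is a smaller risk. A patient who learns the arm and then withdraws or refuses the blood sample has no visit 1 D-dimer, and so cannot be placed in any of the groups that define the first primary outcome.

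**Working it through.** **1. What the text fixes about order.** The protocol has no figure on this point to reproduce. Its sample size does not depend on the order of events within visit 1. The check is therefore a reading of the relevant sections together.

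| Section | What it settles | What it leaves open |
|---|---|---|
| Randomisation | Eligibility and consent come before the code; the code is immediate once details are entered | Whether the details include any baseline measure |
| Trial intervention, Visit 1 | Consent, randomisation and all assessments share one visit; randomisation is described first | No sequencing word links randomisation to the assessments |
| Trial intervention, Visit 1, last sentences | Group O has a later D-dimer test | The phrase that seems to put allocation after the assessments is also used in Randomisation for the moment the code is issued |
| Sample size | The grouping D-dimer is done at the randomisation visit, unlike the later Group O test | Whether it is done before or after the code |

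No section places a visit 1 measure before the code. A site could follow the release rule exactly and take the subjective baselines with the arm known.

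**2. Possible size for the QALY.** Three inputs are assumptions:
- EQ-5D is available at 0, 6, 12, 18 and 24 months (the protocol says six-monthly for two years).
- QALYs are computed by the trapezoidal rule.
- Knowledge of the arm creates a between-arm difference d in the baseline EQ-5D only, with d from 0.01 to 0.03.

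The trapezoidal weights in years are 0.25, 0.5, 0.5, 0.5 and 0.25, which sum to 2.

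- *No baseline adjustment.* Only the baseline term is wrong, so the error is 0.25 × d. For d = 0.01 this is 0.0025; for d = 0.03 it is 0.0075.
- *Full change-score adjustment.* The baseline is subtracted over the whole 2 years, so the error is 0.25d − 2d = −1.75d. In size this is 1.75 × 0.01 = 0.0175 to 1.75 × 0.03 = 0.0525.

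The two errors have opposite signs. If stopping warfarin lowers the baseline answers in Group O, the unadjusted analysis slightly favours continuing, and the change-score analysis favours stopping by seven times as much (1.75/0.25 = 7). Adjustment, which normally helps, is where the damage is larger.

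**3. PTS and VEINES.** The documents give nothing from which to size a shift in these scores, so none is offered.

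**The case against.** The strongest objection is that the order of steps within one visit is operational detail, which a condensed article may leave to the full protocol. Paragraph order is not procedural order, and the details entered before the code could include the baselines. This is right as far as it goes. A reader might infer that every baseline in the trial is a post-randomisation measure, but the documents do not say so. What remains is that the article does state a release rule, and that rule contains no baseline condition.

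Three other stronger readings are tempting and are not supported:

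- *Ineligible patients will be randomised.* Visit 1 describes the interview on history and medication after randomisation, while Assessment of safety treats a medical and drug history as screening. But allocation requires eligibility, the notes are checked beforehand, a physician signs off, and nothing says the interview and the screening history are the same event. This is wording to reconcile. The exclusions in Table 1 for conditions found later are a separate matter that reordering visit 1 would not cure.
- *The D-dimer groups are biased.* A value drawn minutes after allocation, with the result concealed, would hardly change. Only refusal or withdrawal after learning the arm remains, and its frequency is unknown.
- *Nothing except D-dimer is blinded.* The Independent Adverse Event committee is blinded to allocation.

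It is also fair to say that the protocol names neither a baseline-adjusted QALY nor a change-from-baseline analysis, so the larger figure applies only if such a method is used.

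**Conclusion.** The point holds in limited form. The protocol does not require the visit 1 baselines to be complete before the open allocation is known, and the order in which it describes the visit suggests that they may not be. The exposed results are PTS incidence and severity, change in quality of life, and the cost-utility analysis.

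The QALY figures of 0.25d and 1.75d show the mechanism and rest on an assumed d; they are not an estimate of actual bias. The primary comparison of recurrence is largely unaffected, because events must be radiologically documented and the committee reviewing hospital admissions and deaths is blinded. The exception is any patient lost between allocation and sampling. The change should be made, but the trial's main answer does not depend on it.

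**What to change.** State in both Trial intervention (Visit 1) and Randomisation that the order is: consent; history, including concomitant medication, and final eligibility confirmation; blood samples; Villalta, VEINES and EQ-5D; then randomisation. Set the existing electronic CRF to release the code only when these fields are complete and the samples are logged as taken, without displaying the D-dimer result.

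The visit, staff and tests are unchanged. The cost is a wording change, one stop in the CRF and a short wait for the code. If sites already work in this order, one sentence in the protocol settles the point.
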